#### *Exclusion criteria*:

Patients with more than 30 min of loss of consciousness for the current episode;Patients with more than 24 h of post-traumatic amnesia;Glasgow Coma Scale score lower than 13 at more than 30 min after the injury;Patients with radiographic evidence of subdural hemorrhage, epidural hemorrhage, intraparenchymal hemorrhage, and cerebral or cerebellar contusion;Post-injury hospitalization for more than 48 h;Fracture (head, neck and spine);Having a neurological condition, other than the actual mTBI;Having a cognitive or behavioural impairment prior to the participation in the study;Have had general anesthesia during the three-month period prior to the study;Having comorbidities of cardiovascular or respiratory systems.

### Randomisation/blinding

A randomisation list will be generated by an independent research assistant (not involved in data collection) prior to the initiation of the study using a random number generator. Allocation will be concealed in sealed and opaque envelopes that will be sequentially numbered. A blocked randomisation will be used to make sure that two equal groups of 23 participants are obtained. Stratification will be done according to sex to ensure women and men are equally represented in each group as it has been shown that women tend to recover more slowly than man from a mTBI [6, 27]. Given that it is not possible to blind the treating physiotherapist and the participants, a single-blind design will be used as only the evaluator will be blinded. One of the Principal Investigator (PI) will open the randomisation envelope indicating the participant’s assignment and will send the information to the treating therapist. The physiotherapists, neuropsychologists and the kinesiologists will be blinded to the baseline evaluation results. To evaluate the effectiveness of blinding, the evaluator will answer the following question at the week-6 evaluation: *“In your opinion, which intervention did this participant received?”* The possible answers are: 1) SPA program (control group); 2) SPA combined with cervicovestibular rehabilitation program (experimental group); 3) I have no idea. Participants will be unaware of the treatment provided to the participants in the other group. Evaluation will be done in a separate site than the intervention site and participants will be instructed not to reveal or discuss treatment with the evaluator.

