### Statistical analyses

Descriptive statistics will be used for all outcome measures at each measurement time to summarize results. Baseline demographic data will be compared (independent *t*-test and Chi-squared tests) to establish the comparability of groups. All data will be tested to check the distributional assumptions for the inferential statistical analyses. An intention-to-treat analysis will be used in which all participants will be analysed in the group to which they were originally assigned. Per protocol analysis will also be performed. All dropouts and the reason for dropping out of the study will be reported. Any harm or unintended effects during the programs will be recorded. A 2-way ANOVA (2 Groups [Group 1 or 2] × 4 Time [week 0, 6, 12, 26]) will be used to analyse the effects of the rehabilitation programs on the primary outcome and on most of the secondary outcomes (SPSS 22, proc. GENLIN). We expect no group effects, as the groups should be equal at baseline. A time effect should be observed, as both groups should improve given they will both receive an interventions. Finally, we expect a significant Time x Group interaction since the groups should react differently over time, ***with a faster recovery for the Experimental group mainly seen at week 6 and 12***. This will be statistically detailed with post-hoc tests (Bonferroni correction). An independent t-test will be used to analyse the effects of the rehabilitation programs on clearance to return to function.

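### Randomisation is stratified by sex as a prognostic factor, but the stated analyses leave sex out; if sex matters as the plan assumes, some efficiency is lost

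*Protocol article*

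**What the plan says.** In the protocol article, Randomisation/blinding fixes two features of the allocation. The first is blocking: "A blocked randomisation will be used to make sure that two equal groups of 23 participants are obtained". The second is the stratum: "Stratification will be done according to sex to ensure women and men are equally represented in each group". The reason given is prognostic, namely that "women tend to recover more slowly than man from a mTBI". Sex is the only stratification factor named.

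The Statistical analyses section sets out the outcome analyses. It states: "A 2-way ANOVA (2 Groups [Group 1 or 2] × 4 Time [week 0, 6, 12, 26]) will be used". This applies "on the primary outcome and on most of the secondary outcomes". The hypothesis rests on the interaction: "we expect a significant Time x Group interaction since the groups should react differently over time", followed by Bonferroni-corrected post-hoc tests. For the remaining outcome, "An independent t-test will be used to analyse the effects of the rehabilitation programs on clearance to return to function". None of these analyses names sex as a factor, covariate or stratum. Sex could enter only the comparison of baseline demographics, which does not adjust the treatment effect.

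**The concern.** Stratified blocking removes the part of the between-arm variation that is due to sex. A model without sex does not take account of this: the sex variance stays in the error term and the standard error is computed as if sex could still differ by chance between arms. When sex is prognostic, the confidence interval is then wider than the design warrants and the test rejects less often than its nominal level.

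The trial has little power to spare. With 23 per group, effect size 0.8 and a two-sided 5% test, power is 75.6% before any attrition, against the planned 80%. Efficiency that can be recovered without recruiting anyone is worth having.

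**Working it through.** **Inputs from the article.** Total 46, 23 per arm (Randomisation/blinding). Alpha 0.05 with sidedness not stated, effect size 0.8, power 0.80, SD 20 PCSS points, attrition 10% (Population). Model terms Group and Time; t-test for clearance (Statistical analyses).

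**Assumptions, because the article gives no figure.** Size of the sex effect (shown as a range), 50% women, sex-stratified blocks of 4, a two-sided 5% test and, for the change contrast, a correlation of 0.5 between visits.

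**The plan's own figure.** With a one-sided test at effect size 0.8, the t-test needs 21 per group, and 21 × 1.1 = 23.1; the normal approximation needs 20, and 20/0.9 = 22.2, rounded up to 23. So 23 is reproduced one-sided. Two-sided, the t-test needs 26, and 26/0.9 = 28.9, rounded up to 29. The two-sided power at 23 per group is therefore 75.6%.

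**Comparison at one time point.** Fix the total SD at 1. With half women, a sex difference of δ SD accounts for δ²/4 of the variance. The model without sex overstates the standard error by the factor 1/√(1 − δ²/4):

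- δ = 0.2: 1/√0.99 = 1.005
- δ = 0.5: 1/√0.9375 = 1.033
- δ = 0.8: 1/√0.84 = 1.091
- δ = 1.0: 1/√0.75 = 1.155

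Simulated trials of 46 patients (6,000 per setting for power, 10,000 for type I error) agree:

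| Sex difference | PCSS points at SD 20 | SE ratio | Type I error, without → with sex | Power, without → with sex |
|---|---|---|---|---|
| 0.2 SD | 4 | 1.005 | 5.0% → 5.0% | 75.4% → 75.8% |
| 0.5 SD | 10 | 1.03 | 4.4% → 5.1% | 76.6% → 78.5% |
| 0.8 SD | 16 | 1.09 | 3.2% → 5.0% | 77.3% → 82.4% |
| 1.0 SD | 20 | 1.16 | 2.6% → 5.1% | 78.3% → 86.3% |

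The gains are 0.4, 1.9, 5.1 and 8.0 points. With 42 patients analysed, roughly the expected number after attrition, the picture is the same: 72.2% → 74.1% at 0.5 SD and 73.1% → 78.9% at 0.8 SD. This arithmetic applies to a group comparison at a single visit and, with days to clearance treated as a continuous outcome, to the clearance t-test.

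**Time x Group contrast.** Take week 6 minus baseline, with SD 1 within sex at each visit and correlation 0.5. The within-sex variance of the change is 2(1 − 0.5) = 1.

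- A sex effect that is constant over time cancels from the difference. The simulated standard error is 0.293 with or without sex, and power is unchanged apart from simulation noise.
- A sex x time effect of γ SD adds γ²/4 to the variance of the change, so the standard error without sex is larger by √(1 + γ²/4): √1.0625 = 1.031 at 0.5 SD and √1.16 = 1.077 at 0.8 SD. The simulated standard errors are 0.302 against 0.293 (ratio 1.03) and 0.317 against 0.293 (ratio 1.08).
- Power without → with sex x time is 74.6% → 74.8% at 0.2 SD, 72.5% → 74.6% at 0.5 SD and 70.0% → 74.8% at 0.8 SD. Type I error at 0.8 SD is 3.2% → 4.5%.

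**The case against.** Several counter-arguments deserve weight.

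- **Adding sex only as a main effect would not help the primary test.** This stands. A constant sex effect drops out of within-person contrasts, so the interaction's standard error does not move. The remedy has to contain sex x time, or work visit by visit with baseline adjustment.
- **The sex effect may be small.** This stands. The article gives no size. One of the two references cited for sex is used in the Background for paediatric cases, whereas the trial enrols adults aged 18 to 65. A sex difference of 0.8 SD would be as large as the treatment effect the trial is sized for. At 0.2 SD the loss is negligible.
- **The stated purpose of stratifying is balance, and balance is kept.** This also stands. A reader might infer that the benefit of stratifying is thrown away, or that the omission biases the estimate or inflates false positives. The document supports none of these. The allocation still balances sex, and with total SD held fixed the unadjusted power itself rises with the sex effect, from 75.4% at 0.2 SD to 78.3% at 1.0 SD.
- **Covariates are commonly left to the analysis plan, and the named procedure accepts them.** This carries less weight. The article states the factors, their levels, the software procedure, the post-hoc correction and the clearance test. A two-way ANOVA with both factors named and a two-sample t-test have no place for a stratum, so adding sex later would change the stated analysis.

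**Conclusion.** The point holds as a conditional loss of efficiency. On the plan's own premise that women recover more slowly, leaving sex out makes the clearance test and single-visit group comparisons conservative. Because slower recovery is a sex effect that changes over time, it makes the Time x Group test conservative too. The size depends on a sex effect the article does not give: nothing of note at 0.2 SD, about 2 power points at 0.5 SD, and about 5 points at 0.8 SD for both the single-visit and the change contrast. The 8 points at 1.0 SD apply to the single-visit comparison only.

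A reader might conclude outright that all standard errors are too large and that power is certainly lost. That goes too far. If sex has little effect, or for the interaction a constant one, nothing is lost. The validity of the trial is not in question; this is a refinement worth making because it is nearly free.

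**What to change.** In Statistical analyses, state that outcome models include the randomisation stratum. For the PCSS and the other continuous outcomes, add sex and sex x time to the Group x Time repeated-measures model, or fit a baseline-adjusted model at each visit with sex as a covariate. For clearance to return to function, adjust the comparison for sex or stratify it by sex. Settle this before outcome data are seen by group, so that adjusted and unadjusted results cannot be chosen between afterwards.

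The cost is about four degrees of freedom in the repeated-measures model: one for sex and 4 − 1 = 3 for sex x time. Sex must already be known to randomise, so no data, visits or patients are added; only the analysis wording changes.

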## Methods

### Study design

This single-blind, parallel-group RCT will include 8 supervised treatments during a 6-week rehabilitation program and four evaluation sessions over 26 weeks (baseline, week 6 [immediately after the rehabilitation program], week 12 [6 week after the end of the rehabilitation program] and week 26). All participants will take part in the baseline evaluation. After giving informed consent, they will first complete a questionnaire on sociodemographic (age, gender, type of sport or physical activities, number of years playing sport and/or other activities), symptomatology (mechanism of injury, history of previous mTBI, history of dizziness, headache, neck pain and unsteadiness) and comorbidity, as well as self-administered questionnaires that evaluate symptoms and functional limitations, including the PCSS (primary outcome). Once baseline data are collected, participants will be randomly assigned to a control or an experimental group. The control group will receive a 6-week gradual sub-threshold physical activation (SPA) program. The experimental group will receive a gradual SPA program combined with a cervicovestibular rehabilitation program. Between week 6 and week 12, participants will be asked to continue their exercises and follow the advice given at the last meeting with the health professional. Six, 12 and 26 weeks after randomization, all the outcomes will be revaluated (see Table 1). The evaluation sessions will be carried out at the *Centre interdisciplinaire de recherche en réadaptation et en intégration sociale* (CIRRIS) by a research assistant blinded to group assignment, while the interventions will be given at *Clinique Cortex* by experienced physiotherapists, neuropsychologists and kinesiologists. Recruitment began on April 1st 2019 in Quebec City, Canada. See Table 1 for Schedule of enrolment, interventions, and assessments. Ethics approval has been obtained from the Sectorial Rehabilitation and Social Integration Research Ethics Committee of the CIUSSS-CN (#2018–619)*.* The study protocol has been registered on ClinicalTrials.gov [NCT03677661–09/15/2018 - version 1].

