### Population

Forty-six adults with a diagnosis of mTBI (based on the definition of McCrory et al.) [5] and symptoms of dizziness, neck pain and/or headaches (reported on the PCSS) [21] lasting for more than 3 weeks will be recruited. Sample size calculation is based on changes evidenced by the PCSS for individuals with mTBI. According to sample size calculation (G*Power 3.1.9.2; α = 0.05, effect size = 0.8, power [1-β] = 0.80, SD = 20.0 PCSS points, MDC = 12.3 PCSS points [22], 10% attrition), a minimum of 23 subjects is needed in each group. The expected attrition (10%) is based on the drop-rate in previous RCT from our group [23–26] and is more than the observed drop-out in similar studies in this population (6% [19] and 2% [20]). Therefore, 46 participants with mTBI will be recruited. Potential participants will be recruited at *Clinique Cortex* (an interdisciplinary concussion clinic specialized in the management of mTBI; 500 new patients with mTBI are evaluated every year), in medical clinics around Quebec City, and through the electronic mailing list of the students and employees at *Université Laval* (> 52,000 individuals).

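### A Principal Investigator opens every envelope from a blocked, sex-stratified list and so sees the running allocation: an avoidable exposure to prediction of later assignments, not a shown bias

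*Protocol article*

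**What the plan says.** All of the procedure is in the protocol article, Methods, Randomisation/blinding, unless noted.

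- Generation: "A randomisation list will be generated by an independent research assistant (not involved in data collection) prior to the initiation of the study".
- Concealment: "Allocation will be concealed in sealed and opaque envelopes that will be sequentially numbered".
- Restriction: "A blocked randomisation will be used to make sure that two equal groups of 23 participants are obtained". The block size, and whether it varies, are not given.
- Strata: "Stratification will be done according to sex to ensure women and men are equally represented in each group".
- Blinding: "Given that it is not possible to blind the treating physiotherapist and the participants, a single-blind design will be used". Only the evaluator is blinded; treating staff do not see the baseline results.
- Opening: "One of the Principal Investigator (PI) will open the randomisation envelope indicating the participant’s assignment and will send the information to the treating therapist".

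Study design places assignment after consent and baseline data, and has the interventions delivered at one specialised clinic. Population names that clinic as one recruitment source, alongside other medical clinics in the area and a university mailing list. One inclusion criterion allows clinical judgement (for example tenderness or reduced motion on the cervical examination). The article does not say who screens, judges eligibility or enrols.

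**The concern.** Sealed, opaque, numbered envelopes stop anyone from reading the next assignment. They do not stop anyone from inferring it from the earlier ones. In a blocked list the arm that is behind within a stratum is the better guess for the next place, and the person who opens every envelope holds the full history of both sex strata.

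If that person, or someone told by that person, influences who is approached, accepted or deferred, the arms can differ in prognosis before treatment starts. Assignment after baseline does not prevent this, because such a choice would be made earlier. Nor does the blinded evaluator, who protects outcome assessment and not selection. With 46 participants and a self-reported primary outcome, a modest selection effect would be hard to tell from a treatment effect.

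**Working it through.** **The plan's own figure.** The list is meant to end at 23 per group. The sample size in Population (effect size 0.8, alpha 0.05, power 0.80, 10% attrition) gives 23 by the one-sided normal formula: 2 × (1.645 + 0.842)² / 0.8² = 19.3, so 20; 20 / 0.9 = 22.2, so 23. The sidedness is a separate matter and does not bear on this point.

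**Inputs.** From the article: 46 participants, 1:1, blocked, two sex strata. Assumed, because not stated: the block sizes, and the sex split (14 to 32 women, or a share of women of 0.5 to 0.7).

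**Guess rate within one block.** The rule is to guess the arm that is behind in the stratum, with a coin flip if tied. For a block of 4, the expected correct guesses at places 1 to 4 are:

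- place 1: 1/2
- place 2: 2/3
- place 3: 1/3 × 1 + 2/3 × 1/2 = 2/3
- place 4: 1

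The sum is 2.833, and 2.833 / 4 = 70.8%. For a block of 2 it is (1/2 + 1) / 2 = 75%. In fixed blocks the arm that is behind is also the arm with more places left, so knowing the block size does not raise the guess rate. What it adds is certainty about some places: a share of 1 / (b/2 + 1) for block size b.

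| Blocks within sex (assumed) | Correct, complete blocks | Correct, 46 participants simulated | Certain if size known |
|---|---|---|---|
| 2 | 75.0% | 74.5% | 50% |
| 4 | 70.8% | 70.0% | 33% |
| 6 | 68.3% | 67.3% | 25% |
| 8 | 66.6% | about 65% | 20% |
| one block of 22 or 24 | about 61% | not run | about 8% |
| random 2/4/6 | not run | about 69.5% | none if undisclosed |
| random 4/6/8 | not run | 67.1% | none if undisclosed |

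The simulated rates are slightly lower because the last block in each stratum may be unfinished. Someone who does not see past assignments scores 50%.

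**Does blocking within sex secure 23/23?** No sex quota is stated. Since 46 is even, the numbers of women and men are both even or both odd.

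- Blocks of 2: both even gives 23/23 for certain; both odd leaves one half-filled block per sex, and these cancel with probability 1/2. With women uniform on 14 to 32 (10 even and 9 odd values): (10 × 1 + 9 × 1/2) / 19 = 76%.
- Blocks of 4: both even leaves one stratum stopped halfway through a block, balanced with probability 2/3; both odd cancels with probability 1/2. (10 × 2/3 + 9 × 1/2) / 19 = 59%.
- Blocks of 6: about 51% by simulation (50% to 54% across the assumed sex splits).

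**Cost of imbalance.** Two-sided t-test, d = 0.8, 44 degrees of freedom, noncentrality 0.8 × √(n₁n₂/46). For 23/23 this is 0.8 × √11.50 = 2.713, power 75.6%. For 21/25 it is 0.8 × √11.41 = 2.703, power 75.3%. For 20/26 power is 74.9%. With random 4/6/8 blocks the simulated imbalance was at most 6, and 2 or fewer in at least 95% of trials.

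**The case against.** The strongest reply is that the harmful link is missing. Bias needs the person who sees the tally to affect enrolment, and the article never gives a PI that role. A condensed article may leave the enrolling role and the block size to the full protocol, and not publishing the block size helps concealment. The plan also has real safeguards: an independent list maker, sealed opaque numbered envelopes, assignment after baseline, and a blinded evaluator. Recruitment is not confined to the treating clinic. Predictability above chance is common to blocked lists, and random block sizes barely change it. Finally, the assistant who makes the list could know every future assignment, and is said only to stay out of data collection.

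Most of this stands, and it limits the point. It does not touch what the article does state, namely that a PI opens each envelope.

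Three stronger readings are tempting and not supported:

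- That a PI can foresee most assignments with certainty. This needs small fixed blocks of known size; the article states neither the size nor that it is fixed.
- That enrolment will be selective. No one is said both to see the tally and to enrol.
- That the bias can be sized. If every guess steered enrolment by an assumed 2 to 5 PCSS points of prognosis, 70% correct guesses would give a group difference of 2 × shift × (2 × 0.70 − 1) = 1.6 to 4.0 points. Neither the shift nor the steering is in the document, so this is an illustration and not evidence.

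**Conclusion.** The point holds as a cheap improvement to a stated procedure. Opening the envelopes gives a PI the running allocation in each sex stratum, and with it a guess rate above 50% for every block size examined: about 65% to 75% for assumed blocks of 8 to 2, and about 61% for one large block per sex of known size. That selective enrolment could follow rests on the further assumption that someone with this knowledge influences recruitment or eligibility. Without that, the bias is zero. The document allows no estimate of its size.

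The stated assurance of two groups of 23 is a small inaccuracy. It is not met in about a quarter to a half of simulated trials with blocks of 2 to 6, but the loss of power is negligible and no result depends on it.

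**What to change.** In Randomisation/blinding, replace the sentence on envelope opening. The independent research assistant who generates the list, stated to take no part in recruitment or eligibility, keeps the envelopes in one series per sex. Once eligibility and baseline data are recorded, this person opens the next envelope in the participant's series and sends the arm directly to the treating therapist. No PI or other person involved in recruitment or eligibility handles the envelopes or sees the running tally. The order after baseline is already in Study design; the new elements are the person and the separation of roles.

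If the blocks are of fixed size, vary them at random within sex and do not disclose the sizes. This removes assignments that are certain in advance but hardly lowers the guess rate (about 69.5% for random 2/4/6 against 70.0% for fixed blocks of 4), so the change of person matters more. As a minor edit, write that about 23 participants per group are expected.

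The cost is one reassigned task, regeneration of any unused envelopes, and a possible imbalance of a few participants (power 75.6% at 23/23 against 75.3% at 21/25). The exposure is reduced and not removed: treating staff at the clinic, which also recruits, will still know the arms of those they treat.
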